#### Change in Tampa Scale of Kinesiophobia

The Tampa Scale of Kinesiophobia contains 17 questions assessing fear of movement, fear of physical activity and fear avoidance, with four Likert responses range from strongly disagree (score=1) to strongly agree (score=4).^35^ Total score ranges from 17 (no kinesiophobia) to 68 (severe kinesiophobia).

### Other measures

Other measures are assessed at baseline and 3 months unless indicated otherwise.

#### Shoe wear time

Shoe wear time is determined using an Orthotimer temperature microsensor. The sensor detects rapid peak changes above ambient temperature and has been previously been shown to be an accurate method for assessing adherence to wearing foot orthoses.^36^ The sensor is positioned within a small (~15 mm × 10 mm) hole cut in the inferior aspect of the arch region of the shoe insole and secured with rigid strapping tape. Participants then walk while wearing the shoe with the sensor in situ to ensure it is comfortable and cannot be felt, with adjustments made to its positioning if necessary. The microsensor is returned by the participant after 3 months using a prepaid express post box, and total wear time is extracted. The number of minutes spent wearing the study shoes, and the number of minutes spent playing sport or exercising while wearing the study shoes, is also self-reported each day during the last week in months 1, 2 and 3 in monthly logbooks.

#### Self-rated adherence with footwear

Participants self-report how much of the time they wore their study shoes during planned sport and exercise-based activities over the previous week, using a 5-point Likert scale, with response options ranging from ‘not at all’ to ‘all of the time’. Participants will complete this scale on the last day of each month for the first 3 months. Participants that indicate they wore the study shoes ‘all of the time’ or ‘most of the time’ during planned sport and exercise-based activities are classified as adherent. All other respondents are classified as not adherent.

#### Cointervention use

Participants complete a custom-developed table at baseline and 3 months to indicate the use of a range of medications and other treatments for their patellofemoral pain over the prior 3 months. Participants who indicate they have used a medication/supplement at least once per week over the past 3 months will be reported as a user of the relevant medication. Participants who have used any other treatment at least once in the past 3 months will be reported as a user of that treatment.

#### Adverse events

Adverse events are defined as any problem experienced in the study knee or elsewhere in the body deemed by the participant to be a result of participating in the trial AND at least one of (1) caused increased pain and/or disability for 2 days or more, (2) resulted in the participant seeking treatment from a health professional and/or (3) caused the participant to miss one or more planned sports or activity sessions. Adverse events are self-reported by participants at 3 months using a custom-developed table. Participants will also be advised that if they experience an adverse event, they can contact the study researchers at any time. A member of the research team ([name], a study podiatrist) will manage any adverse events reported by participants.

#### Number of participants who stopped wearing the study shoes

Participants are asked to indicate whether they stopped wearing the allocated shoes during the study at the 3-month follow-up visit on a categorical scale (yes or no). Participants who indicate ‘yes’ are asked to describe when and why they ceased wearing their allocated shoes.

#### Comfort

Participants are asked to rate their level of comfort with wearing the allocated shoes during sport/exercise using an 11-point NRS (where 0=extremely uncomfortable and 10=extremely comfortable) at 3 months.

#### Expectation of treatment outcome

Expectation of treatment outcome is rated immediately post randomisation/shoe allocation using a 5-point Likert scale, with anchors of ‘no effect at all’ to ‘complete recovery’.

#### Physical activity

The Physical Activity Questionnaire for Adolescents^37^ contains eight questions about how many days and hours per week adolescents have performed physical activities over the prior 7 days, scored using different 5-point scales. The final score is the mean of each score from the eight items. The score ranges from 1 to 5, with a higher score indicating a higher level of activity.

#### Current planned sport and exercise-based activity participation

Current planned sport and exercise-based activity participation is determined from a predetermined list of sport and exercise-based activities. Participants select which activities they are currently participating in, and how many hours per week they participate in each activity. This is self-reported in the baseline and 3-month follow-up questionnaires and in the last week of months 1 and 2 monthly logbooks.

#### Descriptive measures

Descriptive measures are recorded at baseline and include height, weight, body mass index, age, sex, gender, ethnicity, duration of symptoms, comorbidities (using the Paediatric Comorbidity Index),^38^ foot posture (using the Foot Posture Index, higher scores indicate a more pronated foot)^39^ and current ‘usual’ footwear characteristics (shoe weight, heel height, pitch, arch support and flexibility).^25^

### Statistical analyses

All analyses will be performed by study biostatisticians and will be described a priori in a statistical analysis plan that will be developed while blinded to group allocation and published on our website before analyses commence. Main comparative analyses between groups will be performed using intention-to-treat including all randomised participants according to their allocated study arm. Multiple imputation will be used to account for missing data if the proportion of missing data for either primary outcome is >5%. For the primary outcomes, differences in mean change in pain and function will be compared between groups using linear regression modelling adjusted for baseline values. The primary hypothesis will be evaluated by obtaining the estimated differences between groups in mean change in pain and function from baseline to 3 months, and multiplicity adjusted two-sided 95% CIs and p values. The trial will be considered successful if either of the primary outcomes shows statistically significant (ie, p<0.025) benefits of minimalist shoes over motion control shoes. Findings will also be discussed with regard to the MCID in pain (1.5 NRS units) and function (10-unit increase out of 100 on the KOOS-child function in sport and play subscale). Similar analyses will be conducted for continuous secondary outcomes. For binary secondary outcomes, groups will be compared using risk ratios and risk differences, obtained using log-binomial regression models. Similar analyses will be conducted to compare footwear-related adverse events. To assess whether the effect of the intervention on the primary outcome of NRS pain is moderated by the prespecified moderators of foot posture or participation in jumping based sports, an interaction term between randomised group and moderator will be included in separate models. Additional sensitivity analyses may be conducted and will be specified a priori in the statistical analysis plan.

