### Sample size calculations

Total sample sizes of 126 (63 per arm) and 112 (56 per arm) are required to detect clinically meaningful between-group differences in our pain and function primary outcomes at 3 months, with 90% power and alpha=0.025 (split between the two primary outcomes). For pain, the minimal clinically important difference (MCID) on a Numerical Rating Scale (NRS) is 1.5 units (out of 10).^23^ For function, the MCID on the Knee Injury and Osteoarthritis Outcome Score for Children (KOOS-child) function in sport and play subscale is 10 (out of 100).^24^ The sample size assumes equal SD of 2.38 (extrapolated from pain measured on a visual analogue scale due to a lack of relevant research in adolescent patellofemoral pain)^20^ and 15^24^ for each outcome at 3 months, respectively, for each group. It also conservatively assumes no correlation (intraclass correlation coefficient=0) between baseline and 3 months, given the lack of adolescent footwear RCT data on which to base assumptions. Allowing for a conservative 20% attrition,^21^ we will recruit 79 people per arm (n=158).

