#### Primary outcomes

In chronic musculoskeletal pain, patient-reported outcomes are considered most important for testing treatment effectiveness. Pain and physical function are (1) recommended to evaluate treatment and improve reporting for patellofemoral pain in the latest international patellofemoral pain consensus statement^3^ and by the International Patellofemoral Research Network,^26^ (2) recommended by the Cochrane musculoskeletal group to allow combining/comparing data between trials and (3) widely used in leading international patellofemoral pain clinical trials.^9 20 27^ Pain and physical function are measured at baseline and 3 months, and the primary outcomes are change in pain and physical function, defined as baseline minus follow-up. We will consider minimalist shoes to be more effective if either of the primary outcomes shows benefits.

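### The primary success rule pairs multiplicity-adjusted p values with the already split alpha of 0.025, so read literally it corrects twice; the plan should state one rule

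*Protocol article*

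**What the plan says.** Three places in the protocol article bear on the decision threshold.

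- **Sample size calculations.** Each primary outcome is sized "with 90% power and alpha=0.025 (split between the two primary outcomes"). The result is: "Total sample sizes of 126 (63 per arm) and 112 (56 per arm) are required". Allowing for 20% attrition gives 79 per arm, 158 in total.
- **Primary outcomes.** Success on one of the two suffices: "We will consider minimalist shoes to be more effective if either of the primary outcomes shows benefits".
- **Statistical analyses.** The primary hypothesis is to be evaluated from the between-group differences in mean change with "multiplicity adjusted two-sided 95% CIs and p values". The sentence that follows sets the rule: "The trial will be considered successful if either of the primary outcomes shows statistically significant (ie, p<0.025) benefits" of the minimalist shoes.

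The article does not name the adjustment method. It does not say whether the p in the success rule is adjusted or unadjusted.

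**The concern.** There are two equivalent ways to control the familywise error for two primary outcomes at 0.05. Either the threshold is split and unadjusted p values are compared with 0.025, or the p values are adjusted and compared with 0.05. The Statistical analyses section takes the p values from the second and the threshold from the first. The only p values it mentions before the rule are adjusted ones, so a reader who follows the text word for word applies the correction twice.

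This is the trial's sole criterion for success, and it can be carried out in two ways. A raw p of 0.02 on one outcome meets the rule if the p is unadjusted. If the p is Bonferroni-adjusted it becomes 2 × 0.02 = 0.04, and the same result fails. The interval and the test can then point in opposite directions on the primary hypothesis. That choice should not be left open until results are known.

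**Working it through.** **Inputs** (Sample size calculations, unless noted)
- Differences to detect: 1.5 NRS units (pain) and 10 KOOS-child units (function).
- SDs: 2.38 and 15, equal in both arms.
- Power 90%, alpha 0.025 per outcome, two-sided (Statistical analyses), 1:1 allocation (Randomisation and blinding), baseline to 3-month correlation 0.
- Normal quantiles: z(0.90) = 1.2816; z(0.9875) = 2.2414 for two-sided 0.025; z(0.99375) = 2.4977 for two-sided 0.0125.

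**Step 1. Reproduce the stated sample size.** n per arm = 2 (z for alpha + z for power)² (SD/difference)².
- Pain: 2 × (2.2414 + 1.2816)² × (2.38/1.5)² = 62.5, so 63.
- Function: 2 × (2.2414 + 1.2816)² × (15/10)² = 55.9, so 56.
- Attrition: 63/0.8 = 78.75, so 79 per arm and 158 in total.

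All three match. Two-sided 0.05 gives 53 and 48, which do not. The design alpha is therefore two-sided 0.025 on the unadjusted p value of each outcome: the split is already in the threshold.

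**Step 2. Threshold under the literal reading.** Assume a Bonferroni adjustment, adjusted p = 2 × raw p. Requiring adjusted p < 0.025 means raw p < 0.0125.

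**Step 3. Power at 63 evaluable per arm.** SE = SD × √(2/63); power = Φ(difference/SE − z for alpha).

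| Outcome | SE | Difference/SE | Power, raw p<0.025 | Power, raw p<0.0125 |
|---|---|---|---|---|
| Pain | 0.4241 | 3.537 | Φ(1.296) = 90.2% | Φ(1.040) = 85.1% |
| Function | 2.6726 | 3.742 | Φ(1.500) = 93.3% | Φ(1.244) = 89.3% |

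The noncentral t version of the last column gives 84.0% and 88.4%.

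**Step 4. Sample size to keep 90% per outcome at 0.0125.**
- Pain: 2 × (2.4977 + 1.2816)² × (2.38/1.5)² = 71.9, so 72.
- Function: 2 × (2.4977 + 1.2816)² × (15/10)² = 64.3, so 65.
- Recruited: 72/0.8 = 90 per arm, 180 in total, against the planned 158.

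**Step 5. Familywise error.**
- Independent outcomes: 1 − (1 − 0.025)² = 0.0494 with one correction; 1 − (1 − 0.0125)² = 0.0248 with two.
- Assumed outcome correlation 0.5 (bivariate normal): 0.0465 and 0.0236.

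**Step 6. Where the interval and the rule disagree.** A Bonferroni-adjusted 95% CI is a 97.5% CI per outcome, so it excludes zero when raw p < 0.025. Success would need raw p < 0.0125. On the planned SDs and 63 per arm, the zone of conflict is an observed difference of:
- Pain: 2.2414 × 0.4241 = 0.95 to 2.4977 × 0.4241 = 1.06 NRS units.
- Function: 2.2414 × 2.6726 = 5.99 to 2.4977 × 2.6726 = 6.68 units.

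**Step 7. Power for the actual criterion, at least one outcome.** With both true effects at the MCID and 63 per arm:

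| Assumed outcome correlation | Raw p<0.025 | Raw p<0.0125 |
|---|---|---|
| 0 | 99.4% | 98.4% |
| 0.3 | 98.5% | 96.9% |
| 0.5 | 97.6% | 95.5% |
| 0.7 | 96.5% | 93.8% |

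**The case against.** The strongest reply is that double correction is inferred, not stated. The phrase about multiplicity adjustment may attach only to the CIs, with plain p values beside them. Or the adjustment of the p values may simply be the 0.025 threshold. The sample size section supports either reading, because it uses the same 0.025 as the split alpha. On these readings there is one correction, an adjusted 95% CI agrees with p<0.025, and the power is as stated. This stands: a reader might infer that the plan does correct twice and fails to deliver its 90% power, but the text does not settle which p is meant.

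The figure of 0.0125 also needs a Bonferroni-type adjustment, which the article does not name. The method may properly be left to the analysis plan. This stands too, so the figure is conditional.

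Even on the literal reading the loss is limited:
- Only pain falls clearly below 90%.
- The zero baseline correlation is deliberately conservative, while the model adjusts for baseline. With an assumed correlation of 0.3 or 0.5, pain power at 0.0125 is about 88% or 94% (noncentral t).
- With no attrition (79 per arm) pain power is 92.8%.
- Power to succeed on either outcome stays high (Step 7).

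A reader might also conclude that a Holm procedure is required. It is not. A fixed split is valid, and Holm's first step is the same test at 0.025, so it does not change the chance of meeting the either-outcome rule.

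The reply does not remove the mismatch itself. The article fixes both the adjusted p values and the 0.025 in adjacent sentences, and an analysis plan that copied them would inherit the conflict.

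**Conclusion.** The wording is wrong as it stands and should be corrected before analysis. The adjusted p values and the 0.025 threshold belong to different versions of the same correction.

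- **If the p in the rule is adjusted (literal reading, Bonferroni assumed):** power at 63 evaluable per arm is about 85% for pain against the stated 90%, and about 89% for function against the 93% it would have with one correction. Roughly half the intended familywise error is left unused. The CI and the rule conflict for raw p between 0.0125 and 0.025.
- **If the p is unadjusted:** the 90% power and N=158 stand, and the only fault is the description of the p values.

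Type I error is not inflated on either reading. Either-outcome power is about 94% to 98% on the literal reading, given both effects at the MCID and assumed outcome correlations from 0.7 down to 0. The problem is an ambiguous decision rule with a conditional, moderate loss of power. It is not a threat to the trial's validity.

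**What to change.** State one rule in the analysis plan, and use it in the results template:

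- **Option A:** unadjusted two-sided p<0.025 for each primary outcome, reported with 97.5% CIs. This matches the sample size calculation directly.
- **Option B:** multiplicity-adjusted p<0.05, with the adjustment method named and the matching simultaneous 95% CIs.

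In either case remove the pairing of adjusted p values with 0.025. With a Bonferroni adjustment the two options give the same decisions. Holm may be used if the sponsor prefers it, but nothing here depends on it.

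The cost is one sentence, with no extra participants and no change to N=158. The article says the analysis plan will be developed blinded to allocation and published before analyses commence, and it expects recruitment to finish by June 2026. The correction can therefore be made there, before any result is seen.

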## Discussion

The SHAPE trial will be the first RCT to compare the efficacy of minimalist shoes to motion control shoes in adolescents with patellofemoral pain. We hypothesise that minimalist shoes, worn during all planned sports and exercise-based activities over 3 months, will be more effective than motion control shoes, for improving knee pain and function in sport and play. We also hypothesise that minimalist shoes will be more effective in improving secondary outcomes than motion control shoes. Biomechanical studies show that minimalist shoes reduce patellofemoral joint contact forces associated with knee pain in adults,^14 16 17^ supporting their potential to have clinical benefits. However, the effects of minimalist shoes on pain and function have not been investigated in adolescents. Although a recent feasibility RCT found greater improvements in knee pain in adolescents who wore minimalist-style school shoes to those wearing traditional school shoes,^40^ this study was not powered to compare efficacy and participants continued to wear their regular athletic shoes (which contained an ‘elevated heel’) for sports and exercise activities during the trial.

Adolescents nearly always wear footwear for sporting and other exercise-related activities that exacerbate knee pain, thus athletic footwear represents a novel low-burden treatment option to reduce pain and improve function. Unlike adults, there are no clinical guidelines for managing adolescents with patellofemoral pain. Findings from the SHAPE RCT will provide the first evidence regarding the effects of footwear for managing adolescents with this painful condition. The outcomes of this trial may be used to inform future clinical guidelines for adolescents with patellofemoral pain, improving the clinical management of this important but neglected patient group. Our findings may also be used as an impetus for footwear research in adults with patellofemoral pain or other musculoskeletal pain conditions.

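### A flat p<0.025 for both primary outcomes is valid, but Holm would add about 5 to 6 points of power to show benefit on both at the design assumptions, with family-wise error still within 5%

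*Protocol article*

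**What the plan says.** The protocol article sets the threshold in two places. Under Sample size calculations, each primary outcome is sized "with 90% power and alpha=0.025 (split between the two primary outcomes"). Under Statistical analyses, the trial succeeds if "either of the primary outcomes shows statistically significant (ie, p<0.025) benefits of minimalist shoes over motion control shoes".

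The section on primary outcomes gives the same either-outcome rule: "We will consider minimalist shoes to be more effective if either of the primary outcomes shows benefits". The Discussion words the hypothesis more broadly, that minimalist shoes "will be more effective than motion control shoes, for improving knee pain and function in sport and play".

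Statistical analyses also promises "multiplicity adjusted two-sided 95% CIs and p values". It does not name the adjustment procedure, and it defers detail to an analysis plan that is not shown. No step-down or other sequential rule for the second outcome appears in the article.

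**The concern.** Taken at face value, an outcome is significant only at p<0.025, whatever the other outcome shows. Suppose pain gives p=0.01 and function gives p=0.04. Pain is claimed and function is not. Holm's procedure would allow both claims with the family-wise error still at or below 5%, because once the first null hypothesis is rejected only one remains, and it can be tested at the full 0.05.

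What is at stake is the statement about the second outcome. The Introduction's aim and the Discussion's hypothesis cover pain and function together, and each outcome is separately powered at 90%, so readers will want a verdict on each. The trial's overall success does not depend on this point.

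**Working it through.** **Inputs from Sample size calculations.** Pain: difference 1.5, SD 2.38. Function: difference 10, SD 15. Alpha 0.025 per outcome, power 90%, baseline correlation 0, 20% attrition. The two-sided test is from Statistical analyses.

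**Reproducing the stated sample size.** n per arm = 2 × (SD/difference)² × (z₀.₉₈₇₅ + z₀.₉₀)², with z₀.₉₈₇₅ = 2.2414 and z₀.₉₀ = 1.2816.
- Pain: 2 × (2.38/1.5)² × 3.523² = 62.5, so 63.
- Function: 2 × (15/10)² × 3.523² = 55.9, so 56.
- Attrition: 63/0.8 = 78.75, so 79 per arm and 158 in total.

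All match. The design therefore rests on two-sided 0.025 for each outcome.

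**Rules compared.**
- Fixed split, both claimed: P(both p<0.025).
- Holm, both claimed: P(smaller p<0.025 and larger p<0.05).
- At least one claimed: P(smaller p<0.025), which is the same event under both rules.

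**Model.** The two test statistics are bivariate normal with unit variance. Their means are f × (difference/SD) × √(n/2), where f is the true effect as a fraction of the MCID. At f=1 and n=63 these are 0.6303 × 5.612 = 3.54 for pain and 0.6667 × 5.612 = 3.74 for function. Baseline adjustment with baseline correlation r divides both means by √(1−r²). The critical values are 2.241 (for 0.025) and 1.960 (for 0.05). The document does not give the correlation ρ between the two estimates, so ρ = 0.3 to 0.7 is an assumption.

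**Power to show benefit on both outcomes, ρ = 0.3 to 0.7:**

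| Scenario | Fixed split | Holm | Gain (points) |
|---|---|---|---|
| 63 per arm, full MCIDs, r=0 (design) | 85.1–87.1% | 90.9–91.9% | 4.8–5.8 |
| 79 per arm (no attrition), full MCIDs, r=0 | 93.5–94.3% | 96.5–96.8% | 2.5–3.0 |
| 63 per arm, full MCIDs, r=0.5 (assumed) | 95.1–95.7% | 97.4–97.6% | 2.0–2.3 |
| 79 per arm, full MCIDs, r=0.5 | 98.6–98.7% | 99.4% | under 1 |
| 63 per arm, 80% of MCIDs, r=0 | 59.1–64.6% | 70.0–73.7% | 9.1–10.9 |
| 63 per arm, 60% of MCIDs, r=0 | 27.5–34.9% | 37.9–44.7% | 9.7–10.4 |

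Widening ρ to 0 to 0.9 in the design scenario gives gains of 6.4 down to 3.8 points.

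**Power for at least one outcome** in the design scenario falls from 99.3% at ρ=0 to 94.7% at ρ=0.9, identically under both rules.

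**Type I error** (simulation, 2 million draws).
- Both nulls true: 4.95%, 4.61% and 4.05% at ρ = 0, 0.5 and 0.8, the same under both rules.
- One null true and the other outcome effective: 2.5% under the fixed split, and 4.7%, 4.5% and 4.1% under Holm at the same ρ. As a check at ρ=0, with 90% power on the effective outcome: 0.025 + 0.025 × 0.90 = 0.0475.

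**The case against.** The strongest objection is that nothing here is wrong. An equal split is valid, the thresholds agree across the article, and the sample sizes reproduce. Success means a win on either outcome, and Holm leaves that power unchanged. The power gained belongs to a both-outcomes statement that is neither the success criterion nor the basis of the sample size. All of this stands, so the point is an optional efficiency gain.

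A second objection concerns the text. A reader might infer that the plan expressly keeps the second outcome at 0.025 after the first has won. No sentence says so. The success rule would read the same in a Holm plan, since Holm's first step is also the smaller p value below 0.025, and the procedure behind the promised adjusted p values is not named. The unseen analysis plan may already contain a step-down. What the article does state is a flat threshold and no step-down. A later step-down would have to be prespecified to be credible.

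A reader might also take the loss to be 5 to 10 points in general, or Holm to be free of cost. Neither holds. At the design effects the gain is about 5 to 6 points; gains near 10 need true effects well below the MCIDs. Family-wise error stays within 5%, but the false-claim rate for a single null outcome rises when the other is effective. The article also promises adjusted intervals, and Holm has no simple matching ones. A team that wants tests and intervals always to agree can reasonably keep the split.

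**Conclusion.** The point holds as a cheap improvement, not as an error. As written, a second primary outcome with p between 0.025 and 0.05 cannot be claimed, although the 5% error budget would allow it.

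At the plan's own assumptions, Holm raises power to show both outcomes by about 5 to 6 points, from 85–87% to 91–92%. The gain shrinks to about 2 to 3 points with no attrition or with an assumed baseline correlation of 0.5, and to under 1 with both. It is largest, about 9 to 11 points at 63 per arm, if true effects are 60 to 80% of the MCIDs. These figures rest on a normal approximation, the protocol's SDs and the assumed correlation between the two estimates. That Holm keeps family-wise error within 5% and rejects whatever the split rejects does not depend on the correlation.

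**What to change.** If the analysis plan does not already name a procedure, add before unblinding: the two raw (unadjusted) p values for the primary outcomes will be tested by Holm's procedure; if the smaller is below 0.025, that outcome is claimed and the other is tested at 0.05. Keep the either-outcome success rule and the sample size, and report 97.5% confidence intervals for both outcomes.

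State the two downsides alongside. The 97.5% interval for the second outcome can include zero when Holm rejects (its p value lies between 0.025 and 0.05). The error rate for a single null outcome can rise from 2.5% towards 5% when the other outcome is effective.

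The cost is a sentence or two of text, with no change to recruitment, conduct or data collection. After unblinding the change could not credibly be made.
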